
### Participant population

#### Inclusion criteria

The inclusion criteria are as follows:Males and females aged between 18 to 75 yrs.Serum TSH between 4.01 to 10.00 mU/L with normal free thyroxine levels (9 to 25 pmol/L) on two occasions (on day of admission for AMI and 7 to 10 days after AMI).Acute myocardial infarction diagnosed on admission to hospital (chest pain with dynamic ECG changes or increase troponin enzymes (at least a fourfold increase above the laboratory reference range).

### Exclusion criteria

The exclusion criteria are as follows:Patients on medications that affect thyroid function (levothyroxine, carbimazole, propylthiouracil, amiodarone, lithium).Patients who are unable to provide written informed consent.Patients with advanced malignancy (who, in the opinion of the investigator, are unlikely to survive for more than 6 months).Patients with sustained ventricular tachycardia requiring treatment that occurs >24 hrs after myocardial reperfusion/revascularisation.Patients who have contra-indications to MR scanning (cardiac pacemaker, metallic heart valves, cochlear implants, coronary artery stents incompatible with MR scanning, *etcetera*).Patients who are unlikely or unwilling, in the opinion of the investigator, to attend for study-specific visits.Participants whose serum TSH is >10.0 or <4.0 on either occasion.Patients who are already participating in another interventional study.

### Screening, recruitment and consent

#### Identification, screening and recruitment of participants

Eligible participants will be identified from the cardiology units of acute hospitals in the North East of England (Gateshead, Newcastle, Sunderland, South Tyneside and North Tyneside Hospitals). All individuals who fit the study inclusion and exclusion criteria will have their thyroid function checked, after informed consent is obtained, within 24 hours of diagnosis of AMI. Of these patients, those that have TSH and FT4 levels within the inclusion range will be provided with a participant information sheet for ThyrAMI 2. Furthermore, these individuals will be invited to have a repeat thyroid blood test 7 to 10 days after the day of AMI. The day of AMI is the date of diagnosis or the date of admission to the hospital, whichever is later. Those individuals who have TSH and FT4 levels within the inclusion range on the second occasion will be asked to participate in the study and sign the consent form (Figure 1). Those who do not attend for their second visit blood test will be contacted to enquire whether they are still interested in participating.

Once a participant has had thyroid blood results that are within the desired range for inclusion in the study on two occasions and has consented to participate in the study, the study team will arrange a convenient date and time for the baseline tests and randomisation to the treatment groups (see Figure 2). The dates for the baseline tests will be within 21 days of the patients’ AMI dates.

**Figure 2 Fig2:**
[figure not shown]
**Flow chart representing the levothyroxine post-acute myocardial infarction in patients with subclinical hypothyroidism interventional trial (ThyrAMI 2).**

A screening and recruitment log will be held securely at the Investigator sites. The screening log will document anonymised details of patients invited to participate in the study. A participant recruitment/ID log will record those who consented to participate in the trial.

### Consent procedures

All informed consent discussions will be undertaken by experienced research staff (per delegation log) involved in the study with an opportunity for participants to ask any questions. Following receipt of information about the study (that is, provision of the study invitation pack), participants will be given reasonable time to decide whether or not they would like to participate. Those wishing to take part will provide written informed consent by signing and dating the study consent form and initialling the relevant sections, which will be witnessed and dated by a member of the research team with documented, delegated responsibility to do so. Written informed consent will always be obtained prior to any study specific procedures or investigations, including those necessary to confirm eligibility or arranging any study-specific visits.

The original signed consent form will be retained in the Investigator Site File, with a copy in the relevant clinical notes and a copy provided to the participant. The participant will specifically consent to their GP being informed of their participation in the study. The right to refuse to participate without giving reasons will be respected.

The information sheet and consent form for the study will be available only in English. Interpreters will be arranged for all visits of participants who require them either for verbal translation or for deaf participants wishing to take part in the study, via local NHS arrangements. Qualified interpreters will be used to explain the consent form and information sheet, and great priority will be placed on finding the most direct communication. Participants who lack capacity to consent for themselves will be excluded from the study.

### Intervention

Levothyroxine (LT4) will be used to achieve a target TSH level of 0.4 to 2.5 mU/L.

### Control

A placebo will serve as the control.

#### Randomisation

Participants will be randomised using a computerised randomisation algorithm, stratified by type of MI (NSTEMI versus STEMI), in a 1:1 ratio to levothyroxine therapy or placebo (as container or bottle numbers), starting within 21 (+/− 7) days of the AMI (date of diagnosis or the date of admission to hospital, whichever is later). In addition, investigators will be unaware of allocation and will be blinded to treatment groupings. Randomisation will be administered centrally via Newcastle Clinical Trials Unit using a secure password-protected web-based system.

### Blinding

Assignment to either the LT4 or placebo arm will be blinded to the participant as well as study team (double-blind). Code break envelopes will be available at the pharmacy at each site.

Study medication will be prescribed by the study team at each site using a trial-specific prescription (documenting the required IMP pack number), and dispensed according to local pharmacy practice. Independent study physicians, who will be unblinded, will adjust study drug dose as per protocol. The relevant pharmacy will hold a corresponding list allowing pharmacy staff to correlate IMP pack number with relevant packaged IMP dose for any particular IMP bottle, thus maintaining the double-blind.

At the final visit, the integrity of the blind will be assessed by asking the participants: “It is important for the interpretation of the results of the study that we ask you the following: Do you think you were taking LT4 or placebo? Why do you think this?”

### Study medication

The LT4 medication (IMP) will be used within their licensed indications in this study [29,30]. Nonetheless, since LT4 is being compared to a placebo, additional information is being gathered on the safety and efficacy, and manufacture will involve de-blistering/over-encapsulation; the placebo will be treated as an Investigational Medicinal Product (IMP) for the purpose of this study, and will be labelled and handled accordingly.

The study drug will be sourced, assembled and packaged by Newcastle Specials (Pharmacy Production Unit) at The Newcastle upon Tyne Hospitals NHS Foundation Trust, MIA (IMP) 17136. The LT4 to be used in this study will be generic Levothyroxine 25 mcg and 50 mcg tablets (Amdipharm Mercury Ltd). This will be purchased in blister packs.

The double-blind will be achieved by de-blistering and over-encapsulation, using a capsule filler of Lactose BP. For doses that are multiples of 50 mcg, we will over-encapsulate Levothyroxine 50 mcg tablets; for the remaining 25 mcg, 75 mcg and 125 mcg dose increments, we will over-encapsulate Levothyroxine 25 mcg tablets. This ensures the capsule size is kept as small as possible for swallowing purposes (DB capsules Size A, colour: Swedish orange; manufacturer: Capsugel). Capsules will be re-packaged into an appropriate bottle container (polypropylene) and labelled.

As it is not feasible to predict in advance exactly how much IMP must be packaged per study dose, predictions will be based on known current doses as per routine clinical practice; production run(s) will generate surplus stock per IMP dose. The LT4 medication will have a shelf-life maximum of 24 months (less any reduction in expiry due to the shortest expiry date of blister packs purchased). The IMP should NOT be stored above 25 °C and must be stored in the original container to protect it from light and moisture, as per the clinical trial label. A temperature log will be maintained as per local pharmacy procedures, and appropriate IMP storage will be guaranteed until the IMP arrives in patient possession.

The side effects of LT4 (25 mcg and 50 mcg) are well known and documented [29,30]. The total daily dose provided to each participant will be between 25 mcg and 150 mcg.

### Administration of the study drug

Participants will be randomised to either LT4 or placebo to be taken orally once daily. This will be discussed at the time of consent and will be clear in the patient information sheet. Initial starting dose of LT4 will always be 25 mcg daily. To achieve the desired target TSH levels in the LT4-treated group (target TSH levels 0.4 to 2.5 mU/L), participants will have their TSH levels checked every 4 weeks and concomitant dose of their LT4 altered by 25 mcg daily, if required. The IMP will be provided as 5 week supplies of LT4 or matching placebo (dispensed separately at each visit), packaged into appropriate individual polypropylene bottles. The label on the bottle will not indicate details of the arm of the study to which the participant has been randomised. The label will instead contain a pack number, which will be the link to the relevant dose.

Study medication will be prescribed by the PI or co-investigator at each site using a trial-specific prescription (documenting the required IMP pack number), and dispensed according to local pharmacy practice. Independent study physicians who will be unblinded will adjust study drug dose as per protocol. The relevant pharmacy will hold a corresponding list allowing the pharmacy staff to correlate the IMP pack number with relevant packaged IMP dose for any particular IMP bottle, thus maintaining the double-blind.

Participants will be informed of potential adverse reactions and advised to contact the relevant study team if required. A study-specific participant contact card will also be provided.

Once randomised, the participant will begin their study medication on Day 0.

At 4, 8, 12 and 24 weeks (+/− 7 days), serum TSH levels will be checked and LT4 doses adjusted as follows (the next bottle of IMP should be started at week 4, 8, 12, 24 +/− 7 days, respectively):

LT4 group:TSH 0.4 to 2.5 mU/L: Continue LT4 at current dose once dailyTSH > 2.5 mU/L: LT4 increased by 25 mcg dailyTSH < 0.4 mU/L: LT4 reduced by 25 mcg, or if already on 25 mcg daily (the lowest possible dose), then recheck TFTs in 4 weeks. If TSH is ≥0.4 mU/L then continue on current dose. Otherwise, if TSH continues to be <0.4 mU/L on the repeat blood test, then the participant will be withdrawn from the study.

Placebo group:Individuals in this group will have a fresh bottle of IMP starting at 4, 8, 12, 24 +/− 7 days after blood tests to maintain the double blind.

LT4 treatment based on the above regimen will continue for a total of approximately 52 weeks at which point the final set of study specific assessments will be made (with a further follow-up phone call at approximately 53 weeks). If a participant in the placebo arm has a TSH >10 mU/L then their TFTs will be rechecked in 4 weeks. If, the TSH is ≤10 mU/L on the repeat test then the participant will continue with the study and, if, the TSH continues to be >10 mU/L then the participant will be withdrawn from the study. At the final visit, participants on each arm of the study will stop their IMP and will be referred back to their GP to have their thyroid function checked in 6 to 12 weeks. The GP and the patient will be encouraged to discuss whether there is a need to commence LT4 therapy in these individuals based on the clinical situation. The GP letter (sent once the participant is randomised) and the GP follow-up letter (sent after each participant completes their IMP) outlines the suggestion to recheck TSH levels at 6to 12 weeks for each participant once they have completed their IMP.

At the end of each visit, participants will be asked to return any surplus study drug in the original packaging to the study team, who will verify and document compliance. All unused study medication and packaging will be sent to the local pharmacy for documentation and destruction as per local policy (following appropriate reconciliation by the Trial Manager). Documentation of prescribing, dispensing and return of study medication shall be maintained for study records.

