**Table 1 Tab1:** **Schedule of events for ThyrAMI 2**

	**Pre-screening**	**Baseline**			**Randomisation**	**follow-up**							
**VISIT**		**1A**	**1B**	**1C**		**2**	**3**	**4**	**5**	**6A**	**6B**	**6C**	**7**
**assessments**	**Within 24 hours of AMI**	**7 to 10 days post AMI**	**Day 0**			**Week 4 (+/− 7 days)**	**Week 8 (+/− 7 days)**	**Week 12 (+/− 7 days)**	**Week 24 (+/− 7 days)**	**Week 52 (+/− 7 days)**			**Week 53 (+/− 7 days)**
Identification and initial approach (including provision of PIS)	X												
Eligibility criteria checked	X												
Written informed consentǂ		X											
Physical examination (height ****, weight, BP, pulse)		X										X	
Venepuncture		X*				X**	X**	X**	X**			X*	
Clinical history (medical history, medication list)		X											
Questionnaires (SF12, MLWHFQ, CES-D) completed		X										X	
Safety checks (ECG, pulse oximetry and NYHA assessment		X				X	X	X	X			X	
Cardiac MRI			X							X			
EndoPat, Badimon chamber, VerifyNow and TEG analysis				X							X		
Randomisation (after written informed consent obtained) and study drug dispensation					X ***#***								
Study medication prescribed and dispensed (following LT4 dose assessment at visits 2 to 5 only)						X	X	X	X				
Study medication compliance checks						X	X	X	X			X	
Concomitant medication						X	X	X	X			X	
Adverse events						X	X	X	X			X	X
Serious adverse events						X	X	X	X			X	X

X* 20 ml blood: TSH, FT4, FT3, TPO antibodies, Total cholesterol, HDL, Triglycerides, serum BNP, endothelial markers (10 ml gel/gold tube and 10 ml EDTA/purple tube).

X** 5 ml blood: TSH, FT4, FT3 only (gel/gold tube).

Height ****: To be measured at baseline visit only (or could be self-reported if apparatus not available; for example at participant’s home).

ǂ After full discussion and answering any questions.

List of Abbreviations:

BP, blood pressure; BTF, British Thyroid Foundation; CES-D, Centre for Epidemiologic Studies Depression Scale; ECG, electrocardiogram; LT4, levothyroxine; MLWHFQ, Minnesota Living With Heart Failure Questionnaire; MRI, magnetic resonance imaging; NYHA, New York Heart Association; PIS, patient information sheet(s); SF12, short-form health survey; TEG, thromboelastography.

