### Compliance and withdrawal

#### Assessment of compliance

Compliance with study medication (IMP) will be assessed and documented by the research team by checking and recording the number of returned capsules at each visit. This allows any issues to be addressed immediately with the participant. Compliance will be classed as good if between 80 to 100%. The local pharmacy will also document all unused study medication/packaging prior to appropriate reconciliation by the Trial Manager.

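### Drug supply, titration frequency and dose range as stated do not agree with the ThyrAMI 2 visit schedule

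*Protocol article*

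**What the plan says.** **Supply.** Under Administration of the study drug: "The IMP will be provided as 5 week supplies of LT4 or matching placebo (dispensed separately at each visit"). On timing: "Once randomised, the participant will begin their study medication on Day 0", and after that "the next bottle of IMP should be started at week 4, 8, 12, 24 +/− 7 days, respectively". The dispensing row of Table 1 reads "Study medication prescribed and dispensed (following LT4 dose assessment at visits 2 to 5 only") and is marked at weeks 4, 8, 12 and 24; the first supply is issued at randomisation. The table shows no dispensing between weeks 12 and 24 or between weeks 24 and 52. The same section has leftover capsules handed back at each visit, has treatment lasting about 52 weeks, and has participants stop study drug at the final visit.

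**Titration.** One sentence in that section says "participants will have their TSH levels checked every 4 weeks and concomitant dose of their LT4 altered by 25 mcg daily, if required". Pharmacovigilance likewise describes 25 mcg increases at 4-week intervals. The operative rule is different: "At 4, 8, 12 and 24 weeks (+/− 7 days), serum TSH levels will be checked and LT4 doses adjusted as follows". Table 1 follows the operative rule, with thyroid bloods at weeks 4, 8, 12, 24 and 52 after randomisation.

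**Dose range.** Under Study medication: "The total daily dose provided to each participant will be between 25 mcg and 150 mcg". The starting dose is 25 mcg and each step is 25 mcg.

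**The concern.** A 5-week pack suits visits 4 weeks apart with a 7-day window (4 + 1 = 5 weeks). It does not suit the 12-week interval from week 12 to week 24 or the 28-week interval from week 24 to week 52. The text appears to combine two schedules, one with 4-weekly contacts and one with four dosing visits and a final visit, without saying which governs supply, TSH checks and dose.

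The primary outcome is LVEF by MRI at week 52, the end of the longest interval. If the amount dispensed at weeks 12 and 24 is not fixed, sites may resolve it differently, and exposure before the primary measurement would then vary for reasons unrelated to the patient. Both arms get their bottles at the same times, so this would not favour one arm. It would, however, leave unclear what duration of levothyroxine the trial compares with placebo. TSH monitoring after a dose change is also a safety matter, and the text gives two incompatible frequencies for it.

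**Working it through.** **Inputs, all from the protocol article.** Bottle starts: weeks 0, 4, 8, 12 and 24. Pack size: 5 weeks. End of treatment: about week 52. Surplus: returned at each visit. Starting dose: 25 mcg. Step: 25 mcg. Stated range: 25 to 150 mcg. Visit window: ±7 days.

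**1. The plan's own figures under the 4-weekly wording.** If checks and dispensing took place every 4 weeks, there would be 13 bottles (weeks 0 to 48). Each would cover its 4-week interval, so 52 weeks are covered with no gap. Reaching 150 mcg takes (150 − 25)/25 = 5 upward steps, and 5 × 4 = week 20. Both stated figures, 52 weeks and 150 mcg, come out.

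**2. Supply under the operative rule and Table 1.** With one bottle per visit and surplus returned, uncovered time = max(0, interval − 5).

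| Interval (weeks) | Length | Covered | Uncovered |
|---|---|---|---|
| 0–4 | 4 | 4 | 0 |
| 4–8 | 4 | 4 | 0 |
| 8–12 | 4 | 4 | 0 |
| 12–24 | 12 | 5 | 7 (weeks 17–24) |
| 24–52 | 28 | 5 | 23 (weeks 29–52) |
| Total | 52 | 22 | 30 |

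Coverage is 22/52 = 42%. Moving every visit, including the last, by up to one week either way gives 28 to 33 uncovered weeks.

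If surplus were kept instead, the total supply would be 5 × 5 = 25 weeks, or 25/52 = 48%. The first gap would shrink to weeks 20–24 and the total gap to 4 + 23 = 27 weeks (26 to 28 with the visit windows).

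For scale only, covering the same intervals with 5-week packs would take 1, 1, 1, 3 and 6 packs, 12 in all, against the 5 dispensings shown.

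**3. TSH checks.** Every 4 weeks up to week 48 is 48/4 = 12 checks. The operative rule lists four, so eight are absent (weeks 16, 20, 28, 32, 36, 40, 44 and 48). After a dose change at week 24 the next scheduled check is 52 − 24 = 28 weeks later. The rechecks described elsewhere are triggered by an out-of-range result already found, so they do not fill this interval.

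**4. Dose ceiling.** With adjustments at weeks 4, 8, 12 and 24, the highest path is 25 → 50 → 75 → 100 → 125 mcg, that is 25 + 4 × 25 = 125 mcg. This is one step below the stated 150 mcg. The 4-week recheck for low TSH on 25 mcg adds no upward step.

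**The case against.** The strongest reply is that the protocol plainly intends 52 weeks of treatment. It says so, and it has participants stop study drug at the final visit, which makes no sense if the drug ran out at week 29. The plural wording about supplies and individual bottles can be read as giving a pack unit, with several packs issued at weeks 12 and 24. Packs per visit are also a detail that an article may leave to a pharmacy manual. This has force: a reader might infer that participants will be without drug for 30 weeks and have their MRI 23 weeks after the last capsule, and the documents do not support that as a planned course. It follows only if exactly one bottle is dispensed per visit. What remains is that the article does address supply. It gives a pack size, a singular next bottle, dispensing visits and return of surplus, and together these do not add up to the stated duration.

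On dose, 150 mcg is an upper bound on what may be provided, and nobody is required to receive it. A reader might infer that it cannot be reached at all. That is true only under the week 4, 8, 12 and 24 rule, so the mismatch follows from the two titration frequencies and is the smaller part of the point.

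Two further inferences should not be drawn. The first is a loss of power: any figure would need both the one-bottle reading and a rule linking effect to weeks on drug, and the documents give no such rule. The second is that capsule counts would record full compliance through a gap. Assessment of compliance says "Compliance will be classed as good if between 80 to 100"% on the basis of returned capsules but states no denominator, so the result cannot be deduced. The denominator is at most a wording clarification.

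**Conclusion.** The concern holds as an internal contradiction in the stated supply, titration and dose provisions. It does not show that an interruption of treatment is planned.

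- **Supply:** one 5-week bottle per listed visit covers 22 of 52 weeks with surplus returned, or 25 if it is kept. This rests on the one-bottle reading, which the singular wording, the dispensing row and the return of surplus favour, but which the 52-week statement contradicts.
- **TSH checks:** two frequencies are stated. The scheduled one leaves 28 weeks unchecked after week 24. This needs no assumption beyond reading Table 1 and the operative rule as written.
- **Dose range:** the ceiling is 125 mcg under the scheduled adjustments, against 150 mcg stated; 150 mcg is reachable at week 20 under the 4-weekly wording.

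Because these provisions fix drug exposure up to the week-52 primary measurement, and also safety monitoring, they should be settled before the first bottle is dispensed.

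**What to change.** Before first dispensing, reconcile Study medication, Administration of the study drug, Pharmacovigilance and Table 1 so that four things agree:

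1. the quantity supplied at each dispensing visit;
2. the dispensing visits themselves;
3. the frequency of TSH checks and dose changes;
4. the stated dose range.

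The quantity supplied should cover every interval up to week 52, allowing for the visit window. Which schedule and which dose range govern is for the clinical team; this review proposes neither. If the full protocol or pharmacy manual already states the number of bottles per visit, carrying that into the text settles the supply part. The titration and dose-range statements would still need to be aligned.

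The cost is a protocol and pharmacy-manual amendment and, depending on the choice made, more capsules per visit or more visits and blood tests. The sample size and the primary analysis do not change.
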